### Data collection

All women that register for prenatal care at a participating center will receive written information about the study. All women under 24 weeks of gestational age (GA) at inclusion who are able to communicate in Dutch (with assistance) will be asked to participate in the study. Their care provider will verbally inform the women at their first prenatal consultation (generally around 8–12 weeks of GA) and will ask them for informed consent. No exclusion criteria will be employed. Participation includes permission to collect women’s routine pregnancy outcomes as registered in the National Dutch Perinatal Data Registry (Perined, see end of this section) and optional agreement to fill out four self-administered questionnaires. For participants under the age of 18, informed consent of their parents or caregivers will be obtained.

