#### Intervention group

Within the intervention period, pregnant women are offered perinatal care in the CP model. In the CP model traditional prenatal care with one-to-one visits with a perinatal care provider is replaced by the use of a group model [35]. Care is provided by a midwife or an obstetrician (facilitator) and a co-facilitator to groups of eight to twelve women of similar gestational age. Groups meet eight to ten times during pregnancy at the usual scheduled visits, with sessions running for 90 to 120 min. The usual prenatal health assessment is integrated with information, education and peer support. All involved care providers will be trained by licensed trainers to perform CP. The intervention period begins when the center starts to recruit for their first CP group, after the randomized time point. All women included in the study during this period will be part of the intervention group. In addition to the study information, participants will be informed about CP at their first prenatal consultation and will be given the choice to participate in CP. Women that do not participate in CP will receive usual individual care, resulting in two sub-groups within the intervention group. See Fig. 1.

We will use data from the Perined database. The Perined database contains linked and validated routine care information concerning pregnancy, delivery, (re)admissions and pregnancy outcomes [36]. Data are routinely and separately registered by midwives, obstetricians, general practitioners and paediatricians/neonatologists. For this study, the Perined data will be complemented with data from the questionnaires to be completed by participating women at four time points: Table 1 provides an overview of the timing of the different items. Reminders will be sent after 1, 2 and 3 weeks and participants will be reminded by their care provider. Finally, we will use implementation data from CP-group-evaluations and qualitative data from semi-structured interviews with care providers. Outcome measurements are described below. More details on instruments used in the questionnaires are provided in Table 2.

**Table 1 Tab1:** Overview of items in the questionnaires at four measurement time points

T1, inclusion (8–12 weeks of GA)	T2 (28 weeks of GA)	T3 (36 weeks of GA)	T4 (6 weeks postpartum)
Basic characteristics, current weight	Life style Knowledge (2)	Life style (3), medication use (2)	Life style (4), prenatal and perinatal health care use (2)

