### Statistical issues

#### Sample size calculation

A minimal sample of 600 pregnant women in both the intervention and control condition is needed to be able to accept with 95% confidence and an upper confidence limit less than 1.85, that after the intervention has been implemented, there is at least no significant difference in infant morbidity (using 14% of infant morbidity as outcome) between CP and individual care. This sample size is also largely sufficient to find amongst others a difference in prenatal care satisfaction or in proportion of breastfeeding comparable to Ickovics et al, with an α of 0.05 and a power of 0.90 [17]. We will account for a 20% loss to follow-up and aim to include in total 1600 women (800 in both conditions).

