#### Data analysis

Data entry will be automatic by using a secured online survey system or (in case of hard copy) scanned and checked using the Teleform software. Data will be stored in a digital data base only accessible to the researchers. Before analysis, all data will be cleaned improving data quality.

We will conduct intention-to-treat analyses to compare the primary and secondary outcomes of the control group with those of the complete intervention group. Also a per protocol analysis will be performed comparing the outcomes of the three subgroups (see Fig. 1): control group (1), CP-participants (2) and non-CP-participants (3). Analyses will be descriptive and inferential (univariate and multivariate), and we plan to perform multilevel techniques to account for the clustering effect among participants in centers and CP-participants in CP-groups. The analysis of the implementation data and health care use will be descriptive. The relation between the degree of implementation and primary and secondary outcomes will be analyzed using multi-level analysis. Furthermore, the interviews with care providers will be conducted using a topic list based on the results of the analysis of the implementation data. They will be transcribed and qualitatively analyzed using a framework approach.

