## Discussion

Former research has shown a positive effect of CP, including a higher birth weight and more prenatal care satisfaction, however the findings were inconsistent [17, 26, 27, 30, 31]. Furthermore, due to differences in population characteristics and health care system, previous findings cannot be directly extrapolated to the Dutch setting. Our study aims to contribute to the evidence regarding the effect of CP and will give a first indication of the effect and implementation of CP in a Western high-income society other than the USA. Also, by measuring factors that are hypothesized to mediate the effect of CP, we aim to be able to explain the mechanisms that lead to eventual found effects on maternal and neonatal outcomes.

A strength of our study lies in the stepped wedge cluster design. In this design, participating practices are randomly assigned to the period in which they will start providing CP and will function as their own control group before implementing CP. Also, it allows to take into account time effects. Another strength of the study is the use of routine data to assess several neonatal and maternal outcome measures.

One limitation however is the fact that centers are not yet trained in CP and that it takes some time to implement, which may lead to less model fidelity and smaller effect sizes. Fidelity to facilitate group processes in CP and content fidelity are known to associate with significant reductions in preterm birth and intensive utilization of care [58]. To gain more insight in the effects of fidelity of the model as provided by health care providers we will collect data on process and implementation, and will relate it to the effects of CP. The possibility of selection bias by letting women choose between CP or individual care is another limitation of our study. To be able to estimate the degree of selection bias, we will collect numerous demographic and psychosocial data of both groups in the intervention period (CP-participants and Non-CP-participants), also allowing us to correct for differences in basic characteristics. In addition, we will perform an intention-to-treat analysis, as well as a per protocol analysis. Differences in results of both analyses will provide an indication of assumed selection bias.

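### The 0.90 power claimed for satisfaction and breastfeeding is not supported for the intention-to-treat contrast unless CP uptake is high or the cited effect is large

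*Protocol article*

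**What the plan says.** The sample size rests on infant morbidity: "A minimal sample of 600 pregnant women in both the intervention and control condition is needed", for a contrast described as "between CP and individual care". The section then adds a secondary claim: "This sample size is also largely sufficient to find amongst others a difference in prenatal care satisfaction or in proportion of breastfeeding comparable to Ickovics", followed by "with an α of 0.05 and a power of 0.90". No means, standard deviations or proportions from the cited trial are given. The Background lists that trial among the randomised trials of prenatal group care. The only allowance is 20% loss to follow-up, with 800 women enrolled per condition.

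Under Intervention group, every woman included after a centre starts recruiting for CP belongs to the intervention condition, but CP itself is her choice: "Women that do not participate in CP will receive usual individual care, resulting in two sub-groups within the intervention group". Under Data analysis, the intention-to-treat analyses will "compare the primary and secondary outcomes of the control group with those of the complete intervention group". A three-subgroup per protocol comparison is planned as well. The share of women who start CP is to be monitored (Process outcomes), but no value is assumed for it.

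Satisfaction is measured by a questionnaire at 36 weeks, and breastfeeding is asked about in the postpartum questionnaire (Table 1). Under Data collection, consent covers registry data plus "optional agreement to fill out four self-administered questionnaires".

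**The concern.** The powered effect and the analysed contrast do not match. The power sentence borrows a difference from a trial of group care against individual care. The intention-to-treat analysis estimates the effect of being offered CP, averaged over women who take it up and women who do not. If decliners gain nothing, the expected difference is uptake times the full difference, and the number of women needed grows with the inverse square of uptake. Nothing in the sample size section allows for this.

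Satisfaction and breastfeeding are the only outcomes named with a stated power; the morbidity calculation gives a confidence limit but no power. A null intention-to-treat result on either could be read as a well-powered failure to confirm the earlier trial, when dilution by women who never attended CP might explain it. The issue is separate from clustering and would remain if women were independent.

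**Working it through.** **Inputs from the article.** 600 women per condition; alpha 0.05 (taken as two-sided, since the article does not say); power 0.90; 800 enrolled per condition; 20% loss.

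**Not in the article, so varied.** The cited difference, CP uptake *u*, agreement to the questionnaires, and any benefit to decliners.

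**1. The plan's own figure.** The 0.90 cannot be reproduced because the cited difference is not stated. What can be found is the smallest difference that 600 per condition detects with 0.90 power:

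(1.960 + 1.282) × √(2/600) = 0.187 SD.

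For proportions, the detectable increase is 9.3, 8.9, 8.2 and 6.9 percentage points from control proportions of 50%, 60%, 70% and 80%.

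**2. Dilution.** Let *n0* be the number per condition that gives 0.90 power for the full cited difference, so that *d* = 3.2415 × √(2/*n0*). With no effect in decliners, the intention-to-treat difference is *u* × *d*, and

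power = Φ(*u* × *d* × √(600/2) − 1.96) = Φ(3.2415 × *u* × √(600/*n0*) − 1.96).

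Power stays at 0.90 only if *u* ≥ √(*n0*/600).

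| *n0* per condition | Full difference (SD) | Minimum uptake for 0.90 | Power at 80% uptake | at 60% | at 50% |
|---|---|---|---|---|---|
| 300 | 0.265 | 71% | 0.96 | 0.79 | 0.63 |
| 200 | 0.324 | 58% | 0.99 | 0.92 | 0.80 |
| 150 | 0.374 | 50% | >0.99 | 0.97 | 0.90 |
| 600 (no surplus) | 0.187 | 100% | 0.74 | 0.49 | 0.37 |

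The last row is only a boundary, because the article claims a surplus.

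**3. Benefit to decliners.** If decliners receive a share *s* of the effect, the factor becomes *u* + (1 − *u*)*s*. With *s* = 0.3 (assumed) and *u* = 0.5 the factor is 0.65. For *n0* = 300, power is Φ(3.2415 × 0.65 × √2 − 1.96) = 0.85 instead of 0.63. The minimum uptake becomes (√(*n0*/600) − 0.3)/0.7, which is 58%, 40% and 29% for *n0* = 300, 200 and 150.

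**4. Questionnaire response.** 800 × 0.80 = 640 women remain per condition. If the 20% already covers refusal of the questionnaires, the minimum uptake is √(*n0*/640) = 68%, 56% and 48% for *n0* = 300, 200 and 150. If refusal comes on top, agreement of 80% leaves 640 × 0.80 = 512 and agreement of 60% leaves 640 × 0.60 = 384. With 512 respondents the minimum uptake is √(*n0*/512) = 77%, 63% and 54%. With 384 it is √(*n0*/384) = 88%, 72% and 63%. The last two sets assume no benefit to decliners.

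**The case against.** - **A reader might infer that the claimed power is not delivered.** The article does not support that. The cited difference and the uptake are both absent, and the power sentence claims a surplus. With a full difference of 0.40 SD, 600 per condition still gives Φ(0.5 × 0.40 × √300 − 1.96) = 0.93 at 50% uptake. The shortfall is conditional. This objection stands.
- **Zero effect in decliners is pessimistic.** The Design section expects CP training to change non-CP consultations too, and gives this as a reason against individual randomisation. The table is therefore a worst case on this point. This also stands.
- **The cited difference may already include non-attendance.** If it compares women as assigned, the relevant factor is uptake here relative to attendance there. The article does not say. Even so, some non-attendance within an assigned group is not the same as an open choice of individual care.
- **A reader might infer that about 94% must agree to the questionnaires**, since 640 × 0.9375 = 600. That does not hold as a requirement. The 600 was set for morbidity and is said to exceed what these outcomes need, and the 20% may already cover non-response.
- **A reader might take the Discussion as conceding the dilution.** Its remark that "it takes some time to implement, which may lead to less model fidelity and smaller effect sizes" concerns fidelity in newly trained centres, not women who decline.
- **The per protocol comparison avoids the dilution, and a null result would be read beside it.** True, but it uses only the women who took part, and the Discussion acknowledges self-selection. It cannot carry a power statement tied to 600 per condition.
- **A condensed article may leave such inputs to the full protocol.** That would excuse silence on uptake. Here the article states a power figure, and its own design text changes the contrast to which the figure applies.

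**Conclusion.** The point holds in a conditional form. The article attaches 0.90 power to a difference from a group-care trial, while its intention-to-treat contrast includes women who choose individual care and no uptake is allowed for. The 0.90 is therefore unsupported for that contrast unless uptake is high or the cited difference is well above the 0.19 SD minimum. The size of any loss runs from none to substantial: at 50% uptake, power is 0.90 if the cited difference needs 150 women per condition and 0.63 if it needs 300. These figures assume independent women, a two-sided 0.05 test, 600 analysed per condition and no effect in decliners. Benefit to decliners would soften them; clustering, or questionnaire refusal beyond the 20% loss, would worsen them. The claim concerns secondary outcomes, and the morbidity calculation that sets the sample size is untouched by this point.

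**What to change.** In the sample size section, restate the secondary power claim for the intention-to-treat contrast:

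- Give the detectable intention-to-treat difference at 600 respondents per condition: about 0.19 SD, or 7 to 9 percentage points for control proportions of 50% to 80%, labelled as before the design effect.
- State the cited difference in figures, and give power for its uptake-diluted value over a stated range of uptake and questionnaire response. Say whether the 20% loss covers women who decline the questionnaires, and what is assumed for women who decline CP.
- If the claim for the undiluted difference is kept, attach it to the comparison of CP-participants with controls, at that subgroup's expected size, and label it non-randomised.

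The cost is wording and a short recalculation, with no extra women. The downside is a less favourable stated power for secondary outcomes.

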#### Data analysis

Data entry will be automatic by using a secured online survey system or (in case of hard copy) scanned and checked using the Teleform software. Data will be stored in a digital data base only accessible to the researchers. Before analysis, all data will be cleaned improving data quality.

We will conduct intention-to-treat analyses to compare the primary and secondary outcomes of the control group with those of the complete intervention group. Also a per protocol analysis will be performed comparing the outcomes of the three subgroups (see Fig. 1): control group (1), CP-participants (2) and non-CP-participants (3). Analyses will be descriptive and inferential (univariate and multivariate), and we plan to perform multilevel techniques to account for the clustering effect among participants in centers and CP-participants in CP-groups. The analysis of the implementation data and health care use will be descriptive. The relation between the degree of implementation and primary and secondary outcomes will be analyzed using multi-level analysis. Furthermore, the interviews with care providers will be conducted using a topic list based on the results of the analysis of the implementation data. They will be transcribed and qualitatively analyzed using a framework approach.

## Discussion

Former research has shown a positive effect of CP, including a higher birth weight and more prenatal care satisfaction, however the findings were inconsistent [17, 26, 27, 30, 31]. Furthermore, due to differences in population characteristics and health care system, previous findings cannot be directly extrapolated to the Dutch setting. Our study aims to contribute to the evidence regarding the effect of CP and will give a first indication of the effect and implementation of CP in a Western high-income society other than the USA. Also, by measuring factors that are hypothesized to mediate the effect of CP, we aim to be able to explain the mechanisms that lead to eventual found effects on maternal and neonatal outcomes.

A strength of our study lies in the stepped wedge cluster design. In this design, participating practices are randomly assigned to the period in which they will start providing CP and will function as their own control group before implementing CP. Also, it allows to take into account time effects. Another strength of the study is the use of routine data to assess several neonatal and maternal outcome measures.

One limitation however is the fact that centers are not yet trained in CP and that it takes some time to implement, which may lead to less model fidelity and smaller effect sizes. Fidelity to facilitate group processes in CP and content fidelity are known to associate with significant reductions in preterm birth and intensive utilization of care [58]. To gain more insight in the effects of fidelity of the model as provided by health care providers we will collect data on process and implementation, and will relate it to the effects of CP. The possibility of selection bias by letting women choose between CP or individual care is another limitation of our study. To be able to estimate the degree of selection bias, we will collect numerous demographic and psychosocial data of both groups in the intervention period (CP-participants and Non-CP-participants), also allowing us to correct for differences in basic characteristics. In addition, we will perform an intention-to-treat analysis, as well as a per protocol analysis. Differences in results of both analyses will provide an indication of assumed selection bias.

Abovementioned limitations of the study are at the same time the strengths of our study, since our chosen design and methods are pragmatic, allowing us to evaluate the effect of CP when implemented in daily practice.

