Research on CP has shown some positive effects: amongst others on health literacy [25, 26], preparedness for labor and birth [17], and initiating breastfeeding [17, 27]. Women reported receiving more social support [28, 29], and were more satisfied with provided care [17, 28–30]. Moreover, the number of preterm births significantly decreased in a high-risk population, the mean birth weight increased and the number of women who received substandard care was reduced [17, 29].

However, a part of the evidence is derived from non-randomized studies. The evidence from randomized controlled trials (RCT) is less obvious, which is due to the limited number of RCT’s on prenatal group-based care and the variation in the reported outcomes [17, 27, 30, 31]. Recently, Caitlin et al. concluded that additional research is required to assess the effects of prenatal group-based care models, such as CP, on neonatal and maternal outcomes [26]. Furthermore, most results of the effect of CP originate from experimental studies conducted in high-risk populations and in the USA [17, 29, 31–34]. It is unknown what the effect of CP is in a different maternity healthcare system and in the general population.

The aim of the present study is to evaluate the effects of CP in the Netherlands in primary health care (low risk population) as well as in hospital based care (moderate to high risk population) on neonatal and maternal health outcomes, health behaviors and psychosocial outcomes. The effectiveness of CP will be established by comparing the outcomes in the intervention group (prenatal care within the CP model) and the control group (usual individual care). Primary hypotheses are that in comparison to the control group, the intervention condition will lead to better neonatal and maternal outcomes. Secondary hypotheses are that the effect on the outcome variables is mediated by (changes in) health literacy, self-regulation, health behavior, health care utilization as well as level of group cohesion and level of implementation.

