## Methods

### Design

This study will be performed in thirteen midwifery practices (primary care, low-risk population) and two hospitals (secondary care, moderate to high-risk population) that do not yet offer CenteringPregnancy within the region ‘northern South-Holland’ (an urban – sub-urban setting). A stepped wedge cluster randomized controlled trial design is chosen for several reasons. Firstly, randomization at individual level is not appropriate, as training professionals in CP will most probably also affect the non-CP consultations. Secondly, since midwifery care in the Netherlands is subjected to marketing forces, cluster randomization is expected to result in unfair competition between independent centers operating in the same region. Within the chosen design, all clusters (midwifery practice or hospital) start to collect control data at the same time (control period). Clusters will subsequently implement the intervention at a different, randomly selected time point and will then start to collect intervention data (intervention period). For this study, we will divide all fifteen centers into three groups and will randomly assign each group to one of three time points (steps) at which they will start to implement the intervention, with a between-step period of 3 months.

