#### Process outcomes

We will assess the implementation of CP by monitoring the percentage of women that start CP, the addressed content within the group sessions, the involvement of women and their partners (adherence), and model fidelity. These data will be collected from the CP-group-evaluations, filled out by the group facilitators at the end of each session. These evaluations also contain data on group cohesion. Women’s experience with CP and their inhibiting and facilitating factors to participate will be addressed in the self-administered questionnaires: see Table 1. Inhibiting and facilitating factors in the implementation process and the care providers satisfaction with prenatal care will be addressed in individual semi-structured in-depth interviews. Health care utilization of women will be measured in the self-administered questionnaires, addressing preconceptional and prenatal utilization of general health care, and health care utilization provided by a perinatal care center.

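### The difference between the ITT and per-protocol results mixes dilution by non-uptake, selection and spill-over, so it cannot by itself indicate selection bias

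*Protocol article*

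**What the plan says.** All women recruited after a centre crosses over belong to the intervention group, whichever form of care they choose. The Protocol article (Intervention group) states: "Women that do not participate in CP will receive usual individual care, resulting in two sub-groups within the intervention group".

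Two analyses follow from this (Data analysis). The ITT analysis will "compare the primary and secondary outcomes of the control group with those of the complete intervention group". The second is introduced as: "Also a per protocol analysis will be performed comparing the outcomes of the three subgroups". Its groups are the control group, CP-participants and non-CP-participants.

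The Discussion names self-selection into CP as a limitation and offers two ways to gauge it. The first is a comparison of choosers and decliners on baseline data: "we will collect numerous demographic and psychosocial data of both groups in the intervention period", with correction for differences in basic characteristics. The second sets the two analyses against each other: "Differences in results of both analyses will provide an indication of assumed selection bias".

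The article does not mention that non-uptake can also separate the two results.

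**The concern.** When women may decline CP, the ITT estimate averages over women who did and did not receive it. If CP works, the ITT effect is smaller than the effect in participants even when choosers and decliners are perfectly comparable. A difference between the two results is then what a successful trial would show, yet the Discussion would have it read as a sign of selection bias. The trial's hypothesis is that "the intervention condition will lead to better neonatal and maternal outcomes", so the reading is least safe when that hypothesis is true.

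At stake is what can be concluded about women who took up CP. A real benefit, diluted in the ITT result, could be put down to selection. Conversely, a small gap could be taken as reassurance when selection is present but masked.

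**Working it through.** **Inputs.** The sentence in the Discussion carries no figure, so there is none to reproduce. From the article: 14% infant morbidity and 600 women per condition (Sample size calculation). Assumed, because the article gives neither: uptake u of 30%, 50% or 70%, and a risk ratio of 0.75.

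**Identity.** Let C, P and N be the risks in controls, CP-participants and non-participants.

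- ITT = u(P − C) + (1 − u)(N − C)
- Participants versus control = P − C
- Gap = ITT − (P − C) = (1 − u)(N − P)

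Let a and b be the risks that choosers and decliners would have under usual care, d the CP effect in choosers (negative if beneficial) and s any spill-over effect in decliners. Then P = a + d, N = b + s, and

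- Gap = (1 − u)[(b − a) − d + s]

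The three terms are selection, CP effect and spill-over. The gap gives only their sum.

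**Case 1: real effect, no selection, no spill-over.** The participant risk ratio is 0.75, and the ITT risk ratio is 1 − u(1 − 0.75). On C = 14%, P = 10.5%.

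| Uptake | Participants RR | ITT RR | RR gap | Gap, percentage points: (1 − u) × 3.5 |
|---|---|---|---|---|
| 30% | 0.75 | 0.925 | 0.175 | 2.45 |
| 50% | 0.75 | 0.875 | 0.125 | 1.75 |
| 70% | 0.75 | 0.825 | 0.075 | 1.05 |

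Selection bias is zero in every row.

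**Case 2: selection only, no CP effect.** Choosers have 0.75 times the average risk. The participant risk ratio is 0.75, the ITT risk ratio is 1.00 and the gap is 0.25 (3.5 points). Here the article's reading is right. Decliners have a risk ratio against control of (1 − 0.75u)/(1 − u): 1.11, 1.25 and 1.58 at 30%, 50% and 70% uptake.

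**Case 3: real effect with opposite selection, 50% uptake.** Let usual-care risks be 16% in choosers and 12% in decliners, so C = 0.5 × 16 + 0.5 × 12 = 14%. With a risk ratio of 0.75, P = 12% and N = 12%. Both estimates are −2.0 points and the gap is 0, although selection is present.

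**What the third group adds.** If the control group has the same mix of would-be choosers and decliners, C = ua + (1 − u)b, so

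- N − C = u(b − a) + s

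The CP effect drops out. This contrast is 0 in case 1, +3.5 points in case 2 (50% uptake: 17.5 − 14) and −2.0 points in case 3 (12 − 14). It separates the cases that the gap cannot, as long as s is small.

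**Precision at 600 per condition.** These figures use 14% risk throughout and make no allowance for clustering or period adjustment. At 50% uptake, SE(N − C) = √[0.14 × 0.86 × (1/300 + 1/600)] = 2.5 points. SE(ITT) = √[0.14 × 0.86 × 2/600] = 2.0 points, so SE(ITT/u) is 4.0 points at 50% uptake and 6.7 points at 30%.

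**The case against.** The strongest reply is that the sentence is a cautious remark in the limitations paragraph. It speaks only of an indication, the Data analysis section attaches no threshold or decision to it, and it follows a planned baseline comparison with adjustment. The ITT contrast stands whatever is made of the gap. The planned third group already allows a better reading, and the choice of estimator for the participant effect can be left to an analysis plan that is not shown.

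Most of this stands, and it rules out three stronger readings that a reader might infer:

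- That the gap arises from non-uptake alone. It can, but only if CP has an effect, and selection alone also produces one (case 2).
- That the article's reading always misleads. With no CP effect and no spill-over, a gap does point to selection.
- That this is the only means offered for judging selection. The Discussion puts the baseline comparison first.

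The hedging does not make the inference valid, however. This is a stated interpretation of two planned analyses, not a detail left open. The baseline comparison reaches measured differences only, so the remark is the one outcome-based check the article describes, and it leaves out the dilution that the design builds in.

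The label per protocol is a lesser matter, because the groups are spelled out. But declining CP is allowed, so decliners have followed the protocol; grouping women by the care they chose is an as-treated comparison.

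**Conclusion.** The point holds in a limited form. The difference between the ITT and participant results is neither specific to selection bias nor reliably sensitive to it, so reading it as an indication of selection can give the wrong conclusion. Under the assumptions above, a risk-ratio gap of 0.075 to 0.175 appears with no selection, a gap of 0.25 appears with selection only, and a gap of 0 can coexist with selection.

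The uptake range and the risk ratio of 0.75 are assumptions. The direction of the result does not depend on them: it needs only a non-zero CP effect and uptake below 100%, and the design provides for women to decline. The planned ITT analysis and the sample size are untouched. What is exposed is the interpretation of the participant results.

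**What to change.** Replace the sentence with a statement that a difference between the two analyses does not by itself indicate selection bias, because non-uptake and spill-over also contribute. If the article stays as it is, put this in the analysis plan and the report. Then judge selection from:

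1. The baseline comparison of participants and non-participants, as already planned.
2. The non-participants-versus-control contrast, already among the planned groups, adjusted for centre and period. It is expected to be null without selection and spill-over.
3. As a sensitivity analysis, the as-treated participant estimate set beside the ITT risk difference divided by uptake. Uptake is already to be recorded (Process outcomes: "monitoring the percentage of women that start CP").

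Describe the three-group comparison as as-treated and observational.

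The cost is wording and one extra analysis, with no new data. The limits should be stated with it. The Design section expects that "training professionals in CP will most probably also affect the non-CP consultations"; such spill-over moves item 2 away from zero without selection and breaks the assumption behind item 3. Items 2 and 3 are also not independent: unadjusted, (P − C) − ITT/u = −[(1 − u)/u](N − C), so item 3 restates item 2 on the participant scale. Both are imprecise, and item 3 especially so at low uptake. A standard error of 2.5 points on item 2 against a 3.5-point difference in case 2 means that a null result would not rule selection out.
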